## Abstract

**Background:**

Currently, patients older than 60 years of age represent 25% of the population and are at an increased risk during surgery. Therefore, reducing postoperative morbidity and mortality is a major concern in medical research and practice. Dependence on caregivers and cognitive impairment represent two major risk factors in the elderly, especially in frail patients after surgery under general anesthesia. In this context, continuous monitoring of the depth of anesthesia using a bispectral index (BIS) sensor may reduce the occurrence of impairments by gaining better control of the anesthetic depth. The first aim of this study is to compare manual versus automated administration of intravenous anesthetics with regard to 6-month functional decline in persons aged 70 years and older. The secondary objective includes an evaluation of the influence of the frail phenotype on self-sufficiency in elderly patients after general anesthesia.

**Methods/design:**

After receiving ethical committee approval and written consent, a complete preoperative assessment of physiological reserve and self-sufficiency will be performed on patients more than 70 years old who are scheduled for surgery under general anesthesia. This evaluation will determine the patient’s frailty status in three categories: robust, pre-frail, and frail. Then, patients will be randomized into two groups: manual administration of anesthetics guided by BIS sensor (manual group) or automated administration (automated group) with recording of the anesthesia. A second examination will be scheduled after 6 months to assess changes in functional abilities, cognitive functions, and frailty status. A priori calculation of sample size gives a population of 430 patients to be included in this multicenter trial.

**Discussion:**

This clinical study is designed to detect any postoperative complications and deaths related to the performance of the general anesthesia guided by the BIS sensor and the preoperative functional status of the elderly: robust, pre-frail, or frail.

**Trial registration:**

ClinicalTrials.gov, NCT02524327. Registered on 10 August 2015.

**Electronic supplementary material:**

The online version of this article (doi:10.1186/s13063-017-1868-9) contains supplementary material, which is available to authorized users.

## Background

In 2010, 16.7% of the French population was over the age of 65, with that number projected to rise to 20% in 2020 according to the National Institute of Statistics and Economic Studies (INSEE). Indeed, this trend is of concern in every developed country. Moreover, progress in surgical techniques and control of anesthesia means that surgical procedures are becoming more common in the elderly, with approximately 30% of surgeries conducted in patients over the age of 70, according to the latest epidemiological surveys. However, aging is accompanied by certain physiological changes that may have a critical impact on the patient’s postoperative outcome, including reduced adaptation in cardiac output to stress, reduced lung compliance, decreased cerebral blood flow, thermal dysregulation, loss of functional units in the kidneys, and decrease in renal blood flow [1].

Increasing age in the general population has led to the development of the concept of frailty to better assess the geriatric patient population [2]. Frailty represents a decrease in homeostasis and resistance to stress, and it increases the vulnerability of a person exposed to the risk of unfavorable changes (morbidity or death) disproportionately in relation to the event [2, 3]. Physiologically, fragility results from the simultaneous impairment or decrease in physiological reserve in multiple systems. The early detection of at-risk individuals is accomplished through geriatric assessments using psychometric scales and the Fried score, which is the most widely used metric scale for frailty and includes five criteria for determining anesthetic or surgical perioperative risk factors. This type of assessment attempts to prevent functional decline and high morbidity and mortality in elderly surgical patients [4, 5]. In this specific situation, a relationship between depth of anesthesia and impaired postoperative outcome has been described in a large but retrospective cohort. This suggested a more pronounced impact on the elderly and especially in pre-frail or frail patients.

The anesthetic risk is increased in the elderly, and a previous survey demonstrated that mortality per 100,000 patients under anesthesia reached 21 in patients 75 years and older, while it was only 5.2/100,000 in patients aged between 45 and 74 years [6]. Considering that anesthesia guided by a bispectral index (BIS) sensor allows the depth of anesthesia to be standardized regardless of comorbidity, the variability of BIS values (oscillations, low values, and the presence of burst suppression) could evoke a window to the brain metabolism and an imbalance between needs and posology. These situations suggesting a possible overdose in anesthetics could have a negative impact on cognitive functions and subsequent postoperative morbidity and mortality. Therefore, identification of these risk factors is essential to provide suitable anesthetic management during surgery. Thus, one of the first lines of therapeutic actions could be the wide use of vasopressors to limit cerebral hypoperfusion and thereby reduce exposure to burst suppression. Another possibility is the use of an automated controller of anesthesia. Our team has previously demonstrated the superiority of a controller versus human-guided anesthesia in maintaining a target of BIS between 40 and 60 while limiting the incidence of too deep anesthesia, which is often associated with the occurrence of a suppression ratio in the elderly [7].

Our hypothesis is that accurate control of the anesthetic depth to limit episodes of too deep anesthesia and burst suppression (isoelectric electroencephalogram (EEG)) could decrease mortality and the occurrence of frailty with a loss of autonomy in the elderly. In the current literature, the absence of such a control leads to a mortality rate of 10% at 6 months in patients more than 70 years old, while the loss of functional capacity approaches 20%, meaning that approximately one third of elderly patients are at risk of experiencing a major negative impact following general anesthesia.

## Methods/design

This study is a multicenter, randomized, single-blinded trial performed with two parallel arms. The trial is recorded as NCT02524327 (available on the website: https://clinicaltrials.gov/ct2/show/NCT02524327), and it received ethical approval from the local committee.

### Eligibility and inclusion

The inclusion criteria included American Society of Anesthesiologists (ASA) grades I–III adults of both sexes more than 70 years old who were scheduled for surgery lasting up to 60 min, living at home or living in institutions without daily medical care, and able to be contacted by phone during the follow-up period. The exclusion criteria included having been diagnosed with dementia or having a severely impaired psychometric test (Mini-Mental State Examination (MMSE) score <15), any disability that would make the geriatric assessment incomplete (visual, auditory, or disabling apraxia), severe brain pathology (tumor, stroke, Parkinson's disease, etc.), or patients with related contraindications for BIS monitoring (pacemaker, brain surgery, cardiac surgery, or any surgery that prevents the analysis of the BIS under suitable conditions).

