### Statistical analysis

The main outcome will be defined as "the percentage of patients alive without loss of autonomy in the sixth month (26 ± 2 weeks) following surgery." By definition, death will be included as a permanent loss of autonomy of the subject. Secondary outcomes include a comparison of the postoperative complications using Dindo and Clavien's classification, a change in the Frail status (subclassified as robust, pre-frail, and frail) after 6 months according to Fried's scale, and the quality of anesthesia assessed through the total duration in the expected interval of BIS value (40–60), the total duration in too deep anesthesia (defined as a BIS value <40), and the occurrence of a suppression ratio. The period of analysis is only that during general anesthesia. Based on the published data, it is estimated that at 6 months, the mortality in this population will be approximately 8%, institutionalization will be required in one in five of the remaining cases, and in the patients who remain alive without institutionalization, a decline in ADL will occur in one subject in six in 6 months. This leads to an overall proportion of patients who will die or whose level of functioning will deteriorate after a scheduled major surgical intervention of 39.4%. We hypothesize that better control of the depth of anesthesia should reduce this figure by one third. Under these conditions, a sample of 430 patients, equally divided between the two anesthesia groups, leads to a Fisher’s exact test with a risk of first species bilateral of 0.05 to a power of 0.8 to highlight the expected difference, if it exists.

This research will include a randomization of 1:1 between the groups with stratification based upon the frailty status of the subject prior to the surgery, as determined using the phenotypic Fried scale in three categories (robust, pre-frail, and frail) crossed with two surgical risks (minor or major) [19] (Table 1). The randomization list with balancing groups is performed using a computer program; allocation to a group is performed automatically.

**Table 1 Tab1:** Determination of surgical risk (minor or major) in the elderly. (Adapted from Eagle [19])

Usual classification	Type of surgery	Adapted classification in elderly patients
Low Risk	Wall surgery without opening the peritoneal cavity	Low Risk
	Abscess drainage	
	Endoscopies	
	Proctology	
	Plastic surgery	
	Ophthalmic surgery	
Intermediate Risk	Intraperitoneal surgery	Major Risk

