	Laparoscopic surgery	
	Endarterectomy	
	Ear, nose and throat (ENT) surgery	
	Prostate surgery	
	Orthopedic surgery	
	*Intermediate risk in elderly (>70 years old)*	
Major Risk	Intermediate surgery performed in emergency	
	Unstable hemodynamic conditions	
	Vascular surgery (aortic and peripheral) and thoracic surgery	
	Prolonged surgery (>4 h) with high fluid displacement or major bleeding	

A statistical intention-to-treat analysis will compare both groups (manual and automated general anesthesia) after 6 months through the generalized linear mixed model (GLIMM), which considers the type of anesthesia, frailty status, and surgery. A significant threshold at 0.05 is defined, and the software used for the analysis will be either R3.0 or SPSS20. A logistic regression or a multivariable analysis could be performed to establish some predictive factors if relevant. To ensure that the hypothesis was correct compared to observed data, an intermediary analysis is planned after 100 inclusions.

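### The inclusion criterion reads as a 60-minute maximum, which conflicts with the >4 h row of the stratification table and with a planning rate stated for major surgery

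*Protocol article*

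**What the plan says.** Three places in the Protocol article bear on the length and type of surgery.

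- **Eligibility and inclusion.** Patients must be "scheduled for surgery lasting up to 60 min". No lower limit on duration is given.
- **Statistical analysis, Table 1.** Randomization is stratified by frailty status "crossed with two surgical risks (minor or major"), and Table 1 assigns operations to those two risk levels. The usual Major Risk class contains "Prolonged surgery (>4 h) with high fluid displacement or major bleeding" and "Vascular surgery (aortic and peripheral) and thoracic surgery". The column adapted for elderly patients also moves the usual intermediate-risk group into Major Risk: intraperitoneal, laparoscopic, ENT, prostate and orthopedic surgery, and endarterectomy.
- **Statistical analysis, sample size.** The planning rate is the share of patients who die or "whose level of functioning will deteriorate after a scheduled major surgical intervention of 39.4" per cent. It is assumed to fall by one third under automated anesthesia. With 430 patients in two equal groups, Fisher's exact test at two-sided 0.05 is said to have power 0.8.

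The Background gives one other overall figure: about one third of elderly patients are at risk of a major negative impact after general anesthesia. That figure is not tied to any length or class of surgery.

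**The concern.** The duration limit decides who enters the trial. Read as a maximum, it admits only operations planned for an hour or less. Read as a minimum, it admits only operations of an hour or more. These two populations barely overlap, and the article supports both: the wording of the criterion gives the first, while the >4 h row and the major-surgery planning rate sit more easily with the second.

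Two things are at stake. First, a site that follows the criterion literally would recruit a population other than the one the trial was sized for. If the event rate there is lower, 430 patients give less than the stated power. Second, centers may apply different rules. The Trial status section says that the first 50 patients have been randomized and that new centers will open shortly, so an ambiguous criterion could mix two populations within one trial.

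**Working it through.** **Step 1: the passages side by side.** A patient scheduled for at most 60 min cannot belong in a row for surgery of more than 4 h (240 min), so under the literal criterion that row holds no patients. The other rows carry no duration. Some of the laparoscopic, ENT, prostate or orthopedic procedures that the adapted column counts as Major Risk could fit within 60 min. The criterion therefore makes one row unreachable but does not by itself empty the stratum.

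**Step 2: reproduce the planned sample size.** Inputs from the Statistical analysis section: p1 = 0.394; p2 = 0.394 × 2/3 = 0.2627; difference d = 0.1313; two-sided alpha 0.05 (z = 1.96); power 0.80 (z = 0.8416). With p̄ = 0.3283:

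n = [1.96·√(2p̄(1−p̄)) + 0.8416·√(p1(1−p1) + p2(1−p2))]² / d²

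= (1.302 + 0.553)² / 0.01725 ≈ 199.5, so 200 per arm (400 in total).

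Continuity correction, which approximates Fisher's test: n′ = (n/4)·[1 + √(1 + 4/(n·d))]² = (199.5/4)·(1 + √1.153)² ≈ 214.5, so 215 per arm, or **430 in total**. Exact enumeration of Fisher's two-sided test at 215 per arm gives power **0.802**. The stated figure is reproduced.

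**Step 3: check the planning rate.** The components are: "the mortality in this population will be approximately 8" per cent; then "institutionalization will be required in one in five of the remaining cases"; then, among those alive and not institutionalized, "a decline in ADL will occur in one subject in six in 6 months". Together: 0.08 + 0.92 × 1/5 + 0.92 × 4/5 × 1/6 = 0.080 + 0.184 + 0.123 = 0.387. This is slightly below 39.4%. At 38.7% the total would be 442 and the power at 430 would be 0.79, so the difference is minor and is not the issue here.

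**Step 4: what if the eligible population has a lower rate?** The article gives no rate for short surgery, so every control rate below the first row of the table is an assumption for this use. The 33.3% value is the Background's general figure of about one third; the others extend the range downward. The one-third relative reduction is kept throughout.

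| Control rate | Automated rate | Exact Fisher power, 215 per arm | Total N for power 0.80 (continuity-corrected) |
|---|---|---|---|
| 39.4% (plan) | 26.3% | 0.802 | 430 |
| 33.3% | 22.2% | 0.70 | 544 |
| 30% | 20.0% | 0.63 | 626 |
| 25% | 16.7% | 0.52 | 792 |
| 20% | 13.3% | 0.41 | 1038 |

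**The case against.** The strongest reply is that Table 1 is only a sorting device. It is adapted from a general surgical-risk classification and also lists intermediate surgery performed as an emergency, although the criterion requires scheduled surgery. A table that already holds one row outside the eligible population may hold another, and an unused row does not break stratification. This stands as far as it goes: the >4 h row alone is weak evidence. It does not answer the sample-size text, which ties the planning rate to scheduled major surgery.

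A second reply is that the rate would not describe the whole sample even with the duration wording settled, because a minor-risk stratum is enrolled on purpose. That is correct, so the power loss cannot be put down to the 60-minute limit alone.

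A third is that an intermediary analysis after 100 inclusions is planned to compare the hypothesis with observed data. It might reveal a low event rate. It would not settle which patients are eligible.

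A reader might also infer more than the article supports:

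- **That the major-risk stratum would empty.** The adapted class includes shorter types of operation, and the article gives no durations for them.
- **That anesthesia would be too short for the arms to differ in depth control.** The article gives no relation between duration and the between-arm difference in BIS control.
- **That 430 is miscalculated.** It reproduces from its stated inputs.

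**Conclusion.** The contradiction is real and lies in the stated text. The criterion sets a maximum that makes the >4 h row unreachable and that does not fit the population for which the 39.4% rate is stated. It needs correction because it governs eligibility, even though the wording change itself is small.

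Confidence is high for the textual conflict and low for its effect on power. If the eligible population has a control rate between 33.3% and 20%, and the one-third reduction holds, power at 430 patients is about 0.70 to 0.41 instead of 0.80. That range is an assumption, not an estimate. The upper end rests on a general figure for elderly patients, and nothing in the article supports the lower end in particular.

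The article does not show whether a minimum or a maximum was intended, nor what the centers have done in practice. It would go too far to conclude that short procedures only have been enrolled, or that the trial is in fact underpowered.

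**What to change.** Reconcile the Eligibility and inclusion section, Table 1 and the sample-size paragraph by stating whether 60 min is a minimum or a maximum. Confirm, center by center, which rule was applied to the patients already randomized.

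- **If it is a minimum:** correct the wording by erratum and notify the sites before new centers open. The cost is one line and a site note; no extra patients are needed on account of the duration wording.
- **If it is a maximum:** align Table 1 with the eligible population, restate the planning event rate for that population (minor-risk patients included), and state the power that 430 patients then give. The cost is a less favorable stated power. Holding power at 0.80 would instead require more patients: 544 to 1038 in total over the assumed control rates of 33.3% to 20%.

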### Frailty status

Although it does not appear systematically during aging, which suggests a genetic component and a role for environmental factors [8], the prevalence of frailty increases with age and ranges from 4% in subjects aged 65–69 years to 26% in subjects older than 85 years. Collard et al. estimated that frailty concerns 10% of people over the age of 65 [9]. Although the concept of frailty is now recognized, there is no consensual definition or screening tool for frailty. Instead, frailty is observed as an accumulation of deficits [10] or as an independent phenotype [4]. In both operational approaches, frailty is defined by the risk of death, functional disability, or institutionalization. Central to this model is the occurrence of sarcopenia, or muscle loss related to age, which is often caused by undernutrition. In this study, we have chosen the model of the frailty phenotype (Fried's scale) resulting from the US Cardiovascular Health Study (CHS), which describes the five operational criteria of frailty. To date, this scale is the most common assessment used in the literature because it allows a quick assessment of an elderly patient by any healthcare provider. The scale is based on the following assessments:Exhaustion. Exhaustion is classified using the Center for Epidemiologic Studies Depression Scale (CES-D) indicator: *I felt that everything I did was an effort; and I could not get going* with the following question: *How often in the last week did you feel this way?* The responses are rated as 0/rarely or none of the time (1 day), 1/some or a little of the time (1–2 days), 2/a moderate amount of the time (3–4 days), or 3/most of the time. Specifically, 1 point is given for subjects answering “2” or “3” to either of these questions.Resistance or aerobic activity (level of physical activity). The quantitative assessment of the energetic expense is performed by using the International Physical Activity Questionnaire-Elderly (IPAQ-E), which distinguishes three levels of activity (low, moderate, and high) according to time spent walking and performing moderate (e.g., carrying light loads, leisurely bicycle rides, or tennis) and vigorous activity (e.g., carrying heavy loads, digging, lifting a pack of six bottles, or speed bicycling) during the past 7 days [11]. Specifically, 1 point is given for low levels of activity.Unintentional loss of weight. Specifically, 1 point is given for a positive response to the question: *Have you lost more than 5 kg in the past year?*
Slow walking. This is measured by determining the time it takes for a patient to walk 4 meters (threshold according to gender and height). Specifically, 1 point is given to any patient with a slow walk.Muscle weakness. This is assessed by evaluating hand grip strength (threshold according to gender and body mass imdex (BMI)). Specifically, 1 point is given if the patient scores below the reference.

At the end of this assessment, a subject is classified as "frail" if the total criteria total more than 3. Subjects with a criterion of 1 or 2 are referred to as "pre-frail," and subjects with no criteria are considered "robust."

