#### Randomization

On day 0, upon arrival at the operating room, centralized randomization on a website will be performed with stratification of the frailty status prior to surgery (phenotypic Fried scale in three categories: robust, pre-frail, frail) crossed with two categories of surgical risk: minor or major. This randomization will determine the modality of total intravenous anesthesia (manual or automated group). For the first arm, total intravenous anesthesia is achieved under the exclusive direction of an anesthesiologist with a BIS value maintained in the range 40–60 as the target — *the manual group* (this is the usual technique used for intravenous drugs). The BIS is an absolute value from 0 to 100 derived from the frontal EEG: 100 corresponding to a fully awake patient and 0 to a flat EEG. The second arm involves completely automated delivery; a proportional-integrative-differential (PID) algorithm is used to manage the administration of both propofol and remifentanil through a controller to reach a BIS target in the range 40–60 — *the automated group*. The PID algorithm means that the controller calculates the difference between the measured output and the setpoint (BIS = 50) to adjust the input value. The algorithm considers the present (proportional), past (integral), and future (derivative) error to adjust for the correction. At any moment, the automatic control can be over-ridden by the physician. This event is recorded for further analysis.

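### The frailty cut-offs leave a patient with exactly 3 of the 5 criteria without a category, although frailty status is a randomization stratum, a model factor and a secondary outcome

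*Protocol article*

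**What the plan says.** Frailty status adopts a phenotype scale that "describes the five operational criteria of frailty" and gives one point for each criterion met, so scores are whole numbers from 0 to 5. The same section then sets three classes:

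- frail "if the total criteria total more than 3";
- "Subjects with a criterion of 1 or 2 are referred to as" pre-frail;
- "subjects with no criteria are considered" robust.

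The classification is used in three places:

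- Randomization specifies "stratification of the frailty status prior to surgery (phenotypic Fried scale in three categories: robust, pre-frail, frail) crossed with two categories of surgical risk"; the two risk levels are minor and major. Statistical analysis repeats this.
- The main model in Statistical analysis is a generalized linear mixed model "which considers the type of anesthesia, frailty status, and surgery".
- The secondary outcomes in Statistical analysis include "a change in the Frail status (subclassified as robust, pre-frail, and frail) after 6 months".

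The Abstract also makes the influence of the frail phenotype on self-sufficiency a secondary objective. Trial status reports that 50 patients have already been included and randomized and that new centers are about to open.

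**The concern.** A rule that sorts patients into strata must give every possible score exactly one class. This one does not, and the gap lies on the boundary between pre-frail and frail, which is the contrast that the frailty objective and part of the Discussion are about. A web randomization system needs one of three frailty levels before it can allocate. For a score of 3, the published rule does not say which level to enter. If the website, the analysis program and the 6-month assessment each close the gap differently, the stratum used at randomization will differ from the covariate in the model. A patient who moves from 2 to 3, or from 3 to 4, would then be counted as changed or unchanged according to an undocumented convention.

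This is not detail that an article may leave to a fuller document. The article states the rule completely, and the stated rule cannot be applied to one of the six possible scores.

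**Working it through.** **1. The plan's own figure.** The only computed design figure is N = 430 (Statistical analysis: control rate 39.4%, reduced by one third, two-sided 0.05, power 0.80, Fisher's exact test).

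- p1 = 0.394; p2 = 0.394 × 2/3 = 0.2627; difference = 0.1313; mean = 0.3283.
- Without continuity correction: n = [1.960·√(2 × 0.3283 × 0.6717) + 0.842·√(0.394 × 0.606 + 0.2627 × 0.7373)]² / 0.1313² ≈ 200 per arm, 400 in total.
- With continuity correction: n′ = (n/4)·[1 + √(1 + 4/(n × 0.1313))]² ≈ 215 per arm, **430** in total.
- Exact Fisher power at 215 per arm: 0.802.

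The figure reproduces. Frailty is not an input to it, so closing the gap leaves it unchanged.

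**2. The rule applied to every score.**

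| Criteria met | Class under the written rule |
|---|---|
| 0 | robust |
| 1 | pre-frail |
| 2 | pre-frail |
| 3 | **none** |
| 4 | frail |
| 5 | frail |

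Five of six scores are classified. There is one gap and no overlap. Three frailty classes × two surgical risks = 6 strata, and a score of 3 fits none of them.

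**3. How many patients (assumption, not an estimate).** The article gives no score distribution. Two quantities have to be assumed.

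*Share with exactly 3 among those with 3 or more.* With independent criteria of common prevalence p, the score is Binomial(5, p) and the share is P(3)/P(≥3). With correlated criteria, a beta-binomial with mean m and intraclass correlation (ICC) is used.

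| Assumption | P(≥3) | Share with exactly 3 |
|---|---|---|
| Independent, p = 0.15 | 2.7% | 0.916 |
| Independent, p = 0.25 | 10.4% | 0.849 |
| Independent, p = 0.40 | 31.7% | 0.726 |
| Beta-binomial, m = 0.20, ICC = 0.1 | 9.8% | 0.746 |
| Beta-binomial, m = 0.30, ICC = 0.3 | 25.6% | 0.475 |

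*Proportion with 3 or more.* Frailty status cites 10% for people over 65. If that carried over to this cohort and counted a score of 3 as frail, 0.10 × 430 = 43 patients.

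The extremes of the share give 43 × 0.475 = 20 and 43 × 0.916 = 39, hence roughly 20 to 40. Not every row agrees with the 10%. The two rows that nearly do give 43 × 0.849 ≈ 37 (independent, p = 0.25) and 43 × 0.746 ≈ 32 (m = 0.20, ICC = 0.1). All of these are scenarios.

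**4. Effect on the treatment comparison.** The primary outcome is being alive without loss of autonomy at 6 months, which is not defined by frailty class. The baseline score is obtained before randomization, so any misplacement of score 3 is independent of arm.

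**The case against.** The strongest reply is that this is a slip of wording. The robust class is closed at 0 and the pre-frail class at 1 or 2, and exactly three classes are required, so frail is the only class left for a score of 3. Randomization is centralized and automatic, a trained neuropsychologist makes the assessment, and the website may hold a correct cut-off that the article does not show. Much of this stands. A slip is the likely origin, and 3 or more is the natural repair. But the condition for frail excludes 3 as plainly as the condition for pre-frail does, and nothing else in the article settles it. A stratification rule should not rest on the reader's guess, particularly with new centers about to open.

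A reader might infer more than the article supports:

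- *That sites are improvising.* Neither the website's coded rule nor the case report form is shown, and Trial status reports no classification problem. Inconsistent handling is possible but not demonstrated.
- *That 20 to 40 patients are in fact affected.* The 10% refers to people over 65 in general, and the Discussion says that the rate of frail patients in the operating room is unknown.
- *That the frail group would almost vanish if score 3 were counted as pre-frail.* Under correlated criteria the share with exactly 3 is about 48% to 75%, so some 25% to 52% of those with 3 or more would remain frail. Near-disappearance needs independent criteria of low prevalence.
- *That the treatment comparison is biased.* Baseline misclassification that is independent of arm may cost some efficiency of stratification and adjustment, but it does not bias the comparison.

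**Conclusion.** The point holds as an error in a stated threshold that the trial relies on. As written, a patient with exactly 3 criteria cannot be placed in any of the six strata, in the frailty factor of the mixed model, or in the 6-month frailty-change outcome. That conclusion needs no assumption.

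The number of patients is not known. The figure of roughly 20 to 40 of 430 rests on three assumptions: that 10% have 3 or more criteria, that this 10% already counts a score of 3 as frail, and that about half to nine-tenths of these patients score exactly 3.

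What is at risk is consistency of strata, covariate adjustment, the secondary objective on the frail phenotype and the frailty-change outcome. The primary comparison of manual with automated anesthesia is not biased, and N = 430 stands. Much of the damage is recoverable if the individual criteria are on record.

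**What to change.** Make the three classes cover every score from 0 to 5. With robust closed at 0 and pre-frail at 1 or 2, the smallest consistent edit defines frail as 3 or more, giving 0 / 1–2 / 3–5. The investigators should confirm that this is what they intended.

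Then:

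- confirm that the randomization website, the mixed model and the 6-month status all use that one rule;
- check how any score-3 patients among those already randomized were stratified, and report it;
- derive the analysis category from the recorded criteria, not from the level entered at randomization, and list any discrepancies between the two.

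The cost is one phrase, one check of the website setting and a re-derivation from recorded data. No new data collection is needed and the sample size does not change.
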